### Randomization

Practices were randomly allocated to care management or usual care in the ratio of 1:1. We performed block randomisation with variable block lengths to ensure study groups of approximately equal size. As population density has shown to have significant impact on hospitalizations [32], cluster randomization was stratified according to population density of the regions of participating practice sites based on a map provided by the Federal Agency of Regional Development Planning [33]. We used computer generated randomization lists (SAS Version 9.2). Separate randomisation lists were prepared for urban and rural practices. Central randomisation was performed by a research assistant who was not involved in the project. PCPs allocation to either intervention or control group remained concealed until patient recruitment in the practice was fully completed. After this, PCPs were informed about their allocation with an official letter from the study coordinating centre.

### Inclusion/Exclusion criteria

#### Practice inclusion and exclusion criteria

Eligible primary care practices had to fulfil the following criteria: Participation in the PC-centred care contract of the AOK-Baden-Württemberg, at least one PCP (e.g. general practitioner or general internist) who was willing to participate in the study, at least one participating HCA, and the ability to perform on-site spirometry and home visits.

Practices which quit participation in the PC-centred care contract of the AOK-Baden-Württemberg during the study will be excluded. Participation in similar clinical trials (e.g. telemonitoring studies) is exempted for participating practices.

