### Recruitment of practice sites and patients

PCPs were eligible for the study if they were participating in the primary care-centred care contract of the General Regional Health Fund (AOK). Participation in the primary care (PC)-centred care contract is voluntary for physicians and patients. Care within this contract implies a gate keeping role of the PCP, PCP training and feedback regarding evidence based pharmacotherapy and patient benefits such as reduced waiting times in the practice and late afternoon consultation hours.

We invited eligible PCPs in the Federal State of Baden-Württemberg (Germany) by a formal letter to participate in the study. 132 PCPs from 115 practices gave their written consent and were randomized into the study groups. 234 PCPs gave information before randomization that they decline to participate due to lack of time (n = 129), practice organization (n = 16), unattractive reimbursement (n = 7), no interest (n = 2), concerns about funding source (n = 1), health status of PCP (n = 4) and plans about giving-up practice in near future (n = 7). 63 PCPs did not further specify their reason for declined participation, whereas 5 PCPs were not able to recruit study patients and withdrew participation before randomization.

From the study coordinating centre PCPs received a list of potentially eligible patients based on inclusion and exclusion criteria (see below). After validation of their eligibility patients were recruited by participating PCPs who were blinded to their allocation to the study groups. Patients not willing to participate were asked to give a reason for their decision (on a voluntary basis). PCPs were asked to document patients screened, asked and not included as well as the reason for inclusion and exclusion.

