### Outcome measures

#### Primary outcome

The number of all-cause hospitalizations per patient during 12 months of follow up will be determined on the basis of insurance claims data.

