### Statistical analysis

Data will be analysed in accordance with the CONSORT statement and its extension for cluster randomised trials [34]. The primary analysis will be performed adhering to the intention-to-treat principle. An additional sensitivity analysis will be conducted on a per-protocol analysis set. Descriptive statistics will be used to summarise characteristics of both practices and patients. A multilevel modelling approach [35] will be applied to evaluate differences between the intervention group and the control group on the primary and all secondary outcomes. This approach will be used to account for the hierarchical structure of the data (i.e. patients nested within practices). Evaluations will include analyses of subgroups based on morbidity, health care utilization and predicted risk of future hospitalization. The effect of the intervention on the primary outcome will be tested at the two-sided significance level of 5%. The result will be presented as the difference between group means with the corresponding 95% confidence interval after adjustment for baseline characteristics. Only the result of this primary efficacy analysis will be interpreted in a confirmatory manner. Interim analyses are not planned. Statistical analyses will be carried out with SAS Version 9.2 (SAS Institute, Cary, NC, USA).

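### The rule excluding practices that leave the insurer's care contract during the study is not confined to the per-protocol set and, read plainly, conflicts with the intention-to-treat primary analysis

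*Protocol article*

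**What the plan says.** Four parts of the protocol article bear on this point.

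- **Practice inclusion and exclusion criteria:** "Practices which quit participation in the PC-centred care contract of the AOK-Baden-Württemberg during the study will be excluded". No analysis set, arm or time limit is attached.
- **Statistical analysis:** "The primary analysis will be performed adhering to the intention-to-treat principle". The per-protocol set has a secondary role: "An additional sensitivity analysis will be conducted on a per-protocol analysis set".
- **Randomization and Recruitment:** the cluster is the randomised unit ("Practices were randomly allocated to care management or usual care in the ratio of 1:1"), and the article reports randomisation as already done: "132 PCPs from 115 practices gave their written consent and were randomized into the study groups". Contract membership can be given up: "Participation in the primary care (PC)-centred care contract is voluntary for physicians and patients". Practices learn their arm once patient recruitment is complete: "After this, PCPs were informed about their allocation with an official letter from the study coordinating centre".
- **Primary outcome:** the number of all-cause hospitalisations over 12 months "will be determined on the basis of insurance claims data". The Data collection section says these data come from the insurer, for participating patients.

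**The concern.** Intention-to-treat in a cluster trial means that every randomised practice, with its recruited patients, is analysed in the arm to which it was allocated. A rule that drops a practice for something it does during follow-up is a different principle. If the exclusion is applied as written, the primary analysis set depends on conduct after allocation is known.

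Two things are at stake. First, if the practices that leave differ in admission rate from those that stay, and leave more often in one arm, the comparison is no longer between the randomised groups. This would affect the only result that the plan will interpret as confirmatory. Second, each exclusion removes a whole cluster of about 17 patients, so precision falls in steps.

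This is more than a detail left to an analysis plan. The article states a rule, and on its plain meaning the rule conflicts with the analysis principle stated elsewhere in the same article.

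**Working it through.** **1. Does the rule reach randomised practices?** The eligibility requirements are written in the past tense, the exit rule in the future tense. The article reports that 115 practices had already been randomised, and the Timeframe section runs follow-up to December 2012. A rule still to be applied therefore falls on randomised practices. As worded, it would even catch a practice that left in 2012, after the 12-month outcome was complete.

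**2. Does any other text confine it?** No. The per-protocol set is mentioned once, without definition. Nothing says that patients of an excluded practice stay in the primary analysis.

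**3. The plan's own sample size (Sample size calculation).** Inputs: difference 0.14, SD 1, two-sided 5%, power 80%, ICC 0.01, 17 patients per practice, 15% drop-out.
- Per arm before clustering: 2 × (1.96 + 0.8416)² × 1² / 0.14² ≈ 801, or 1602 in total.
- Design effect: 1 + 16 × 0.01 = 1.16. Practices per arm: 801 × 1.16 / 17 = 54.7, rounded up to 55. This gives 110 practices and 1870 patients.
- Drop-out: 110 / 0.85 = 129.4, rounded up to 130 practices, and 130 × 17 = 2210 patients.

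All the stated figures reproduce, and none is in dispute.

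**4. Precision.** With k practices in total, split equally, and no other loss, SE = √(2 × 1.16 / (17k/2)) and power = Φ(0.14/SE − 1.96).

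| Practices analysed | Patients | Power |
|---|---|---|
| 115 (as randomised) | 1955 | 82.0% |
| 110 | 1870 | 80.3% |
| 105 | 1785 | 78.4% |
| 100 | 1700 | 76.4% |

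The margin over the 110 practices required is five. The losses of 5, 10 and 15 practices are assumptions.

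**5. Bias, as an illustration.** Let a fraction f of one arm's practices be excluded, and let their patients average e more admissions than the whole arm. With equal cluster sizes, the mean of the remaining practices shifts by −f·e/(1 − f).

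The plan's figures bound e. The between-practice SD is √0.01 × 1 = 0.1. Assume normally distributed practice effects and let exactly the highest-admission practices leave:
- f = 0.10: the mean of the top 10% of a normal distribution is 1.755 SD, so e = 0.176. Shift = −0.10 × 0.176 / 0.90 = −0.020, and 0.020 / 0.14 = 14%.
- f = 0.15: the mean of the top 15% is about 1.55 SD, so e = 0.155. Shift = −0.15 × 0.155 / 0.85 = −0.027, and 0.027 / 0.14 = 20%.

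With 115 / 2 = 57.5 practices per arm, these fractions are about 6 and 9 practices, all from one arm. The shift favours whichever arm loses the practices. Adjustment for baseline characteristics, which the plan intends, could reduce it.

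**The case against.** The best defence is that the sentence sits in an eligibility section and does not define an analysis set. The Statistical analysis section is the only place that does so, and it names intention-to-treat. If exclusion means only that the practice stops taking part and leaves the per-protocol set, the two sections agree. The article is condensed, and the analysis sets may be spelled out in a document not shown. This reading is possible, so the conflict is one of plain wording and not proof of what will be done. But the article does not state that reading, and someone applying the rule as written would delete clusters.

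A reader might go further in four ways that the documents do not support.

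- **Intervention practices will leave selectively because of workload.** The trigger is leaving the insurer's contract, not leaving the trial. Both arms work under that contract, and an overburdened practice could leave the trial and keep it. The 129 of 234 physicians who cited lack of time were declining the trial, so they say nothing about contract exit.
- **The bias could reach 24% or 38% of the target effect.** Those figures need an average excess of 0.3 admissions in the practices that leave, which is three between-practice SDs (0.3 / 0.1). The 38% also treats the 15% allowance for all drop-out as contract exit in one arm. Shifts beyond those shown above would require exit to follow chance variation in patients' realised admissions.
- **Claims will certainly remain available.** The outcome comes from the insurer and nothing ties it to the practice's contract, but the extract covers participating patients. The article does not say whether patients of an excluded practice still count as such.
- **The intervention should stop in these practices.** The article does not address this, and the analysis question does not need it answered.

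**Conclusion.** The point holds as a conflict between two stated rules: an exclusion triggered during the study, with no limit to the per-protocol set, beside an intention-to-treat primary analysis. It deserves correction because it affects the population of the single confirmatory test and could be applied after allocation and outcomes are known.

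The size of any harm cannot be determined from the article, which gives no exit rate and no evidence that exits differ by arm. Open allocation and voluntary contract membership make a difference possible, no more. If exits are few, or unrelated to arm and admission rate, the effect is small. The shift of 14% to 20% of the target difference is near a worst case. It rests on the plan's ICC and SD, normal practice effects, equal cluster sizes, and one-sided loss of exactly the highest-rate practices. Separately, losing more than about five of the 115 practices takes power below 80%, assuming 17 patients per practice and no other loss.

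**What to change.** Reconcile the two sections with one sentence, for example: practices that leave the contract after randomisation, and their patients, remain in the intention-to-treat primary analysis in the arm to which they were randomised, using insurer claims as far as these can be obtained; the exclusion applies only to the per-protocol sensitivity set. The sentence should concern the analysis sets alone and make no statement on whether the intervention continues in such practices.

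The number and dates of contract exits should be reported by arm, so that readers can judge whether a difference arose.

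The cost is small. The planned sample size stays at 110 practices and 1870 patients, and no new data source is needed. The one practical step is to confirm with the insurer that claims for these patients can still be extracted. The Data collection and Primary outcome sections give no reason why they could not.

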#### Patient inclusion and exclusion criteria

To be eligible for the study, patients had to suffer from at least one of the following index conditions: type 2 diabetes mellitus under medical treatment and/or chronic obstructive pulmonary disease under medical treatment and/or chronic heart failure with confirmed diagnosis by a cardiologist. Further inclusion criteria were: High risk for future hospitalization (i.e. predicted likelihood of hospitalization within the upper quartile of the total patient population) and age ≥ 18 years.

The likelihood of at least one hospitalization within the next 12 months (LOH) was calculated on the basis of pseudonymised insurance claims data of all AOK beneficiaries from the participating practices. The software package Case Smart Suite Germany 0.7 (Verisk Health, Munich, Germany) was used to compute LOH. The software calculates LOH on the basis of all ICD10-GM (German modification) inpatient and outpatient diagnosis codes, prior costs and hospital admissions as well as demographic data. All input variables were obtained for a pre-prediction interval of 18 months [15].

Patients with the following criteria were excluded: Active cancer disease (defined as cancer diagnosis under current treatment with radiotherapy or chemotherapy), moderate to severe dementia, permanent residency in a nursing home, participation in a concurrent clinical trial (involving telemonitoring studies), severe physical and mental disorders or other problems that hinder active participation in the intervention (e.g. Non-German speaking patients).

### Data collection

After obtaining written informed consent, patients were registered in the study coordinating centre of the Department of General Practice and Health Services Research Heidelberg (Germany) which is responsible for administration, coordination, data management and monitoring (includes database-set up and validation, data entry, coding, and query management).

Patients will be asked to fill in a pseudonymised paper-based questionnaire. PCPs will document additional data from patients' chart and assess the clinical status of the patient (e.g. dyspnoea, blood pressure). Patient questionnaire and chart review will be performed at baseline, 12-, and 24- month follow-up. In addition to these data sources, pseudonymised insurance claims data of participating patients will be obtained from the AOK including data on health service utilisation, medication, diagnosis and costs. All data from patient questionnaires, case report forms and insurance claims will be compiled.

### Outcome measures

#### Primary outcome

The number of all-cause hospitalizations per patient during 12 months of follow up will be determined on the basis of insurance claims data.

#### Secondary outcomes

Additional information regarding hospital admissions will be obtained from a chart review (planned/un-planned admission) and case report forms. Health-related quality of life will be assessed using the Short Form 12 Health Questionnaire (SF-12) and the EuroQol instrument EQ-5D (see table 1). Other secondary outcome parameters are: Patient Assessment of Chronic Illness Care (PACIC), Medication Adherence (MARS), depression (PHQ-9), self-management capabilities (European Heart Failure Selfcare Behaviour Scale, self-developed scales for DM- and COPD-related self management), physical activity (RAPA), activities of daily living (ADL/IADL), mortality, healthcare utilization (emergency department visits, practice visits, skilled nursing home days) and total healthcare costs. Additionally, clinical parameters will be assessed for all patients (blood pressure), DM-patients (HbA1c, number of (severe) hypoglycaemias, fasting glucose), COPD-patients (MRC dyspnoea sale, forced expiratory volume, number of exacerbations) and CHF-patients (NYHA, number of exacerbations). Qualitative (focus groups with PCPs, HCAs and patients) as well as quantitative (CM documents) process evaluation is planned in order to investigate how the PraCMan intervention is implemented into practice.

**Table 1 T1:** Outcome parameter and instruments of the PraCMan trial

Outcome parameter	Instrument	Data source
**Primary outcome**		

All-cause hospitalizations	Data on admissions	IC

**Secondary outcomes**		

Sociodemographic data	Single items from German standard questionnaire [44]	PQ

Mortality	Patient chart	CRF/IC

Quality of Life	EuroQol (EQ-5D) [45]	PQ

	Short Form 12 Health Questionnaire (SF 12) [46]	PQ

Quality of Care	Patient Assessment of Chronic Illness Care (PACIC) [47]	PQ

Depression	Patient Health Questionnaire (PHQ9) [48]	PQ

Adherence	Medication Adherence Reporting Scale (MARS) [49]	PQ

Physical Activity	The Rapid Assessment of Physical Activity (RAPA) [50]	PQ

Smoking status	Self developed items	CRF

Self-management CHF	European Selfcare Behaviour Scale (EHFScB) [51]	PQ

Self-management COPD/DM	Self developed instrument	PQ

Medication regimen	Pharmacy data	IC

Healthcare costs	Data from hospital care, ambulatory care, nursing facilities, pharmacies, rehabilitation	IC

Activities of daily living	ADL [52] IADL [53]	CRF

Comorbidity	Cumulative Illness Rating Scale (CIRS) [54]	CRF

Home visits/Practice visits	Self developed items	CRF

CHF decompensation (CHF patients)	Self developed items	CRF

COPD exacerbation (COPD patients)	Self developed items	CRF

Hypoglycaemia (DM patients)	Self developed items	CRF

Body mass index	Weight, Height	CRF

Blood pressure (all patients)	Standardized Measurement in the practice	CRF

Fasting glucose	Patient chart	CRF

Hemoglobin-A1c	Patient chart	CRF

Dyspnoea (CHF and COPD patients)	Current NYHA-classification (CHF patients) or current MRC Dyspnoe Score (COPD patients) [55]	CRF

Forced expiratory volume (COPD patients)	Standardized Measurement in the practice	CRF

PQ: Patient questionnaire, CRF: Case Report Form, IC: Insurance claims data.

### Statistical analysis

Data will be analysed in accordance with the CONSORT statement and its extension for cluster randomised trials [34]. The primary analysis will be performed adhering to the intention-to-treat principle. An additional sensitivity analysis will be conducted on a per-protocol analysis set. Descriptive statistics will be used to summarise characteristics of both practices and patients. A multilevel modelling approach [35] will be applied to evaluate differences between the intervention group and the control group on the primary and all secondary outcomes. This approach will be used to account for the hierarchical structure of the data (i.e. patients nested within practices). Evaluations will include analyses of subgroups based on morbidity, health care utilization and predicted risk of future hospitalization. The effect of the intervention on the primary outcome will be tested at the two-sided significance level of 5%. The result will be presented as the difference between group means with the corresponding 95% confidence interval after adjustment for baseline characteristics. Only the result of this primary efficacy analysis will be interpreted in a confirmatory manner. Interim analyses are not planned. Statistical analyses will be carried out with SAS Version 9.2 (SAS Institute, Cary, NC, USA).

## Intervention

PraCMan is a complex care management intervention [36]. Based on the results of a series of exploratory studies [18] a multifaceted intervention was developed to reduce (avoidable) hospitalizations of high risk patients. The intervention consists of three elements:

### Assessment

At the beginning, all patients receive an assessment of medical and non-medical needs and resources using a structured protocol by a practice-based HCA. Contents are: Vaccination status (Influenza, *Streptococcus pneumonia*), allergies, nutritional problems, depression, falls, medication adherence, medication ("brown bag review"), pain, physical activity, smoking status, hearing/seeing problems, constipation, and financial/social situation. In accordance with patient-centred care patients will be asked to prioritise the three most important problems - no matter whether medical or non-medical [37]. The assessment can be performed at a home visit if patients are immobile. Patients with a high risk of falls (determined by the assessment) will receive a preventive home visit by their HCAs in order to identify and remove tripping hazards.

### Planning

At a first step, PCPs and HCAs will discuss the results of the assessment in order to identify needs that can be targeted by care management. These targets will be refined in collaboration with patients and caregivers, if applicable: Patients will be motivated to set long-term goals for CM. Patients and CM teams will then jointly define concrete steps (short-term goals) needed to achieve the long term goals. Self-efficacy to achieve these short term goals will be assessed using a 10-step Likert Scale ("How confident are you that you will take this step during the next XY weeks?"). A 0 displays "absolute no confidence", 10 displays "absolute confidence". If patients rate their self-efficacy lower than 7, concrete steps will be further discussed in order to set a more realistic short term goal. As part of care planning, all patients will receive a patient folder containing disease specific information leaflets, symptom diaries, action plans for self-managing acute exacerbations, a list of diagnosis and allergies, a current medication list, medical reports, lab results, and contact data of the PCP. Additionally, long and short term goals will be documented in the patient folder. The patient is encouraged to take the folder to each medical encounter. The first page of the folder contains a red box for hospital doctors prompting them to call the PCP at least 24 hours prior to discharge. Patients will be trained in the use of the patient folder during their first encounter with their HCA.

